## Introduction

### Background and rationale {6a}

Malignant tumors have become one of the major public health problems that critically threaten the health of the Chinese population. According to the latest statistical data, malignant tumors are the leading cause of death, accounting for 23.91% of all-cause mortality in residents of China [1]. The morbidity and mortality of malignant tumors have shown a constant rise in the past decade [2]. The World Health Organization/International Agency for Research on Cancer (WHO/IARC) released the 2020 Global Cancer Report [3], which states that there were 18.1 million new cancer cases and approximately 9.55 million deaths worldwide in 2018. The latest statistical report by the China National Cancer Center [4] declared that there were 3.929 million new cancer cases and 2.338 million cancer deaths in 2015. The most frequent cancer types included lung, gastric, colorectal, liver, breast, esophageal, and gastrointestinal cancer [5]. In recent years, biomedical discipline has continuously evolved to develop new technologies and methods, and interventional tumor therapy has grown into a comprehensive treatment option for tumor patients owing to its high efficiency, safety, minimally invasive nature, and targetability [6].

Tumor ablation is a common non-vascular interventional tumor therapy and has been recommended by several guidelines for treating diverse solid tumors, for example, liver cancer and lung cancer [7–14]. The guidelines for the treatment of liver cancer recommend radiofrequency, cryotherapy, absolute alcohol injection, and microwave ablation (MWA) as local therapies [8]. These tumor ablation techniques are guided by imaging equipment (such as CT and ultrasound) and puncture needles into the tumor. Acting on the tumor tissue by physical or chemical means makes the tumor tissue necrotic and inactive, so as to achieve the purpose of controlling and eliminating the tumor. In 2018, the number of MWA procedures performed in China has increased to 100,000, accounting for 48% of the global number of these procedures. With continuous progress and development of ablation technology as well as the gradual increase of clinical high-grade evidence, tumor ablation is expected to become one of the preferred methods for treating early-stage solid tumors and an alternative for surgery [15].

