### Eligibility criteria {10}

Patients undergoing tumor ablation procedures are included.

Participants who meet the following inclusion criteria are eligible for this study:Patients who are diagnosed by clinicians and require tumor ablation surgery;Patients who provide written informed consent; andPatients aged 18–80 years.

The exclusion criteria are as follows:Allergy to contrast agents, test drugs, or other ingredients in the drug formulation;History of drug abuse, chronic pain, and mental illness;Use of monoamine oxidase inhibitors within 14 days before randomization;Pregnancy, lactation, and intolerance of surgery for other reasons;Difficulty correctly expressing needs or preferences;Poor compliance, inability to complete the trial according to the study protocol;Participation in other drug trials within 30 days before inclusion; andNot eligible to participate in this trial based on investigator opinion.

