#### Statistical analysis method

The number of included and completed cases in the overall and each site is listed in the case analysis, and three analysis datasets (FAS, PPS, and SS) are generated. Dropouts and excluded cases along with the reasons for their dropping out and exclusion are listed.Demographic and baseline data analysis: Descriptive statistics of demographic data and other baseline characteristic values: For continuous variables, total number of cases, mean, standard deviation, median, and minimum and maximum values are calculated. The t-test will be used for normally-distributed data and the rank-sum test will be used for data with skewed distribution. Frequency and proportion are calculated for countable and grade data. The chi-square test will be used for disordered classification data, and the rank-sum test will be used for ordinal data. Inferential statistical results (*P*-values) are presented based on descriptive statistics.Efficacy analysis:A.Analysis of the primary efficacy indicators (overall response rate): The overall response rate is compared using the chi-square test, corrected chi-square test, or exact probability test. The 95% confidence interval of the difference in response rates between the two groups will be calculated, and if the lower limit of the confidence interval is greater than −10%, the result will be considered non-inferior.B.Analysis of the secondary efficacy indicators: Differences in the scores of NRS at each time point and the total score between the two groups are compared by the *t*-test or rank-sum test; differences in the physician satisfaction VAS score and the nurse satisfaction VAS score between the groups are compared by the t-test or rank-sum test; the difference between the two groups regarding willingness to undergo ablation surgery another time will be compared by the chi-square test, corrected chi-square test, or exact probability test; differences between the two groups with respect to duration of surgery, postoperative hospital stay, and average daily dose will be compared by the t-test or rank-sum test; the difference in the uninterrupted completion rate of surgery without complaints of pain between the groups will be compared by the chi-square test, corrected chi-square test, or exact probability test.Safety analysis: The incidence of adverse reactions will be calculated, their frequency and proportion were systematically listed, and the percentage calculated. A detailed list of cases of various adverse events (AEs), the number and rate of cases, conversion of physical examination indicators, ECG, respiratory and circulatory indicators, and laboratory indicators that “turn normal to abnormal” or “intensify abnormal” after the test, and list clinical explanations will be recorded.

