#### Safety evaluation

##### Observation of AEs

Hypotension (0/1/2): Grade 0: systolic blood pressure (SBP) > 70% or 80/50 mm Hg before surgery; Grade 1: SBP < 70% or 80/50 mm Hg before surgery; Grade 2: SBP < 60% or 70/40 mm Hg before surgery. The patients who develop hypotension are treated with ephedrine.

Heart rate and heart rhythm changes (0/1): 1: heart rate less than 50 beats/min, more than 120 beats/min, or occurrence of arrhythmia; 0: otherwise. Atropine was given for the above conditions.

Hypoxemia (1/2/3/4): Grade 0: 96–100%; Grade 1: 91–95%; Grade 2: 86–90%; Grade 3: < 85%. If Hypoxemia occurred, jaw support was given, and if pulse oxygen saturation was < 90%, oxygen inhalation through a respiratory sac mask was provided.

Upper airway obstruction (0/1/2): Grade 0: no upper airway obstruction; Grade 1: mild snoring but normal oxygen saturation (SpO_2_) maintained; Grade 2: snoring, which must be relieved by oropharyngeal airway or jaw support, or normal SpO_2_ could not be maintained.

Respiratory depression/apnoea (0/1/2): Grade 0: respiratory rate > 12 times/min; Grade 1: 6 times/min < respiratory rate < 12 times/min; Grade 2: respiratory rate < 6 times/min.

Body movement (including retching and swallowing, limb movement) (0/1/2): 0: no body movement; 1: general body movement (toe movement, manual, not affecting the body movement examined); 2: severe body movement (leg movement or hip movement, affecting the body movement examined).

In the Case Report Form, the “Adverse Event Record Form” is maintained, and the investigators record in detail any AEs that occur in the case, particularly those related to analgesic medication. These must be recorded in the original data with medical terms and copied to the Case Report Form. The records of AEs shall include a description of AEs and all related symptoms, occurrence time, severity, duration, measures taken, final result, and outcome.

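### Hypoxemia is graded on absolute saturation with no pre-dose reference, so a patient stable at 91–95% counts as a case after dosing and the contrast between arms is diluted

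*Protocol article*

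**What the plan says.** Under Observation of AEs, in Adverse event reporting and harms {22}, hypoxemia is scored on saturation alone: "Hypoxemia (1/2/3/4): Grade 0: 96–100%; Grade 1: 91–95" per cent, with 86–90% as Grade 2 and below 85% as Grade 3. No pre-operative or pre-pump value enters the definition.

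Hypoxemia is among the adverse reactions that the abstract lists as a primary endpoint, and the Primary safety indicators subsection of {22} names it again.

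Eligibility criteria {10} admits "Patients who are diagnosed by clinicians and require tumor ablation surgery", with consent and an age range of 18–80. The exclusions contain no saturation limit. The nearest are "Pregnancy, lactation, and intolerance of surgery for other reasons" and the investigator's opinion. Background and rationale {6a} says that ablation "has been recommended by several guidelines for treating diverse solid tumors, for example, liver cancer and lung cancer", so patients with lung disease are a plausible part of the population.

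Statistical analysis method, and again Methods for additional analyses {20b}, plans an incidence of adverse reactions. Alongside it comes a tabulation of "respiratory and circulatory indicators, and laboratory indicators that “turn normal to abnormal” or “intensify abnormal” after the test". That tabulation is relative to the patient's earlier state.

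**The concern.** An adverse-reaction rate is meant to describe what happens after the drug is given. A fixed band that starts at 95% cannot separate a patient who fell to 94% from one who was at 94% all along. Both are Grade 1 at the first assessment after dosing.

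The article already uses a change-based standard for respiratory indicators, but only in a separate listing. The same stable reading of 94% would be a hypoxemia case in the incidence table and no conversion in the listing.

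Two things are at stake. The incidence attributed to each drug is too high, and the comparison between nalbuphine and morphine on a named primary safety component looks smaller than it is. Fewer respiratory effects are part of the stated rationale for nalbuphine in {6a}, so a diluted contrast works against a question that the trial wants to answer.

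**Working it through.** **The plan's own figure.** The article gives no assumed hypoxemia rate, so there is none to reproduce. Its one calculated figure is the efficacy sample size: (1.960 + 0.842)² × 2 × 0.9 × 0.1 ÷ 0.10² = 141.3, so 142 per group, and 284 ÷ 0.9 = 315.6, so 316. Both agree with Sample size {14}, and this point leaves them unchanged.

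**The rule applied to one patient.** Take 94% before pump connection and 94% at every later assessment.

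- Observation of AEs: 94% lies in 91–95%, so Grade 1.
- Eligibility {10}: no criterion names saturation, so the patient can be enrolled.
- Statistical analysis method, indicator listing: neither newly abnormal nor worse, so no conversion.

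**Effect on the rates.** Let b be the share of each arm already below 96% before the pump is connected, equal in expectation by randomization. Let p be the new-onset rate among the others. If the baseline patients stay below 96%, the rate under the absolute count is

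r = b + (1 − b)p,

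and the difference between arms is

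r₂ − r₁ = (1 − b)(p₂ − p₁).

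Illustration with p = 10% (nalbuphine) and 20% (morphine). These rates and every b are assumptions; the documents give none of them.

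| b | nalbuphine | morphine | difference (points) | relative risk |
|---|---|---|---|---|
| 0% | 10.0% | 20.0% | 10.0 | 0.50 |
| 5% | 14.5% | 24.0% | 9.5 | 0.60 |
| 10% | 19.0% | 28.0% | 9.0 | 0.68 |
| 20% | 28.0% | 36.0% | 8.0 | 0.78 |
| 30% | 37.0% | 44.0% | 7.0 | 0.84 |

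For example, at b = 10%: 0.10 + 0.90 × 0.10 = 0.19, and 0.10 + 0.90 × 0.20 = 0.28.

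**What a worse-than-baseline count would give.** This depends on how often patients with low entry values worsen.

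- If they worsen at the same rate p as the others, the count gives p itself: 10% v 20%, a difference of 10 points. At b = 10% the absolute count overstates the two rates by 19 − 10 = 9 and 28 − 20 = 8 points and loses one point of difference.
- If none of them worsens, the count gives (1 − b)p: 9% v 18% at b = 10%. The difference is 9 points under either rule, but the absolute count adds 10 points to each arm and moves the relative risk from 0.50 to 0.68.

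The inflated rates and the relative risk closer to 1 appear in both cases. The factor (1 − b) is the shrinkage relative to the contrast among patients with normal entry saturation.

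**The case against.** The strongest reply is that the counting rule is inferred. The article speaks of adverse reactions to opioids, grades events by CTCAE, and records events that occur, with a time of occurrence. Nowhere does it say that every Grade 1 reading becomes an adverse reaction, and how pre-existing findings enter an incidence table is commonly settled in an analysis plan that is not shown. This has some force. But the bands are the only saturation definition in the article, and they call an unchanged 94% Grade 1. The point concerns a definition that is stated, not one left out. If the decision is instead made case by case, it falls to staff who under {17a} are not blinded. That is a reason to write the rule down, not evidence of bias.

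Absolute bands are also ordinary in this section. Respiratory rate is graded on fixed limits, and the hypotension item, "Grade 1: SBP < 70% or 80/50 mm Hg before surgery", mixes a relative and a fixed threshold. So hypotension is not a clean counter-example, and the point does not rest on it. A grading scale and a conversion listing can coexist as separate outputs; the weakness is that only the listing looks at the earlier state.

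A reader might extend the point further than the documents allow:

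- *Heart rhythm.* The item reads "Heart rate and heart rhythm changes (0/1): 1: heart rate less than 50 beats/min, more than 120 beats/min, or occurrence of arrhythmia". Its heading speaks of changes and it scores an occurrence, so long-standing arrhythmia need not count. Only the rate limits are absolute, and neither rate nor rhythm is in the abstract's list of adverse reactions.
- *Cases before the first dose.* Scheduled assessments follow pump connection, and the safety set in {19} requires a post-baseline assessment. The problem is an unchanged value scored after dosing.
- *Loss of power.* The planned safety analysis is descriptive, with counts and percentages. No between-arm safety test is specified, so there is no planned power to lose.
- *Unrestricted entry.* The general exclusions may remove some patients with poor respiratory function, and lung cancer is cited as an example, not as an entry rule.

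**Conclusion.** The point holds for hypoxemia. As written, a patient who enters at 91–95% and does not change meets Grade 1 after dosing, on a named component of the primary adverse-reaction endpoint. Both arms' rates rise, and the risk difference is (1 − b) times that among patients with normal entry saturation: 9 points instead of 10 at b = 10%, and 7 at b = 30%, on the assumed 10% v 20%.

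This rests on an equal baseline share in the arms, on low-entry patients staying below 96%, and on the bands being applied as stated. The share b is unknown, so the real effect may be small. A reader might infer bias in favour of one drug. The documents do not support that, because randomization makes the expected effect dilution in both arms alike.

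**What to change.** Under Observation of AEs, define baseline as the saturation recorded just before pump connection. Count hypoxemia as an adverse reaction only when the grade is worse than at baseline, in line with the indicator listing in Statistical analysis method. Tabulate patients below 96% at entry separately, by arm, so that the baseline share can be seen.

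The cost is a sentence or two of wording. The conversion listing already needs a baseline reading; if saturation is not recorded at pump connection, one value per patient is added. Recruitment has begun, so for patients already enrolled the value would have to come from existing records, and the plan should say how a missing one is handled. The sample size and the management of low saturation are untouched. The downside is that reported hypoxemia rates will be lower than under the absolute count, so the report should state which rule was used.

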### Adverse event reporting and harms {22}

#### Primary safety indicators

Incidence of common adverse reactions to opioid drugs, such as nausea, vomiting, vertigo, constipation, itching, urinary retention, hypoxemia, respiratory depression, drowsiness, delirium, and myoclonus are recorded. AEs are graded 1–5 according to the Common Terminology Criteria for Adverse Events 5.0 (CTCAE 5.0) of the National Cancer Institute (NCI).Grade 1: mild: asymptomatic or mild, clinical or diagnostic findings, no treatment required;Grade 2: moderate: minimal, local, or non-invasive treatment required, limiting age-appropriate instrumental activities of daily living;Grade 3: serious or medically significant but not immediately life-threatening, hospitalization or prolongation of hospitalization indicated, disabling, limiting self-care activities of daily living;Grade 4: life-threatening, urgent treatment required; andGrade 5: death related to AE.

If an AE is not listed in the NCI toxicity grading scale, it can be judged according to the following criteria:Grade I (mild): uncomfortable feeling, but does not affect normal daily activities;Grade II (moderate): uncomfortable degree enough to reduce or affect normal daily activities;Grade III (severe): unable to work or do normal daily activities; andGrade IV (fatal): disabling or fatal.

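### Three safety scales do not place every reading in exactly one grade: respiratory rate 12 has none, hypoxemia codes and grades disagree, and hypotension grades overlap

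*Protocol article*

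**What the plan says.** The scales are in the protocol article under Safety evaluation, Observation of AEs.

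- Respiratory depression: "Grade 0: respiratory rate > 12 times/min; Grade 1: 6 times/min < respiratory rate < 12 times/min". Grade 2 is a rate below 6.
- Hypoxemia: "Hypoxemia (1/2/3/4): Grade 0: 96–100%; Grade 1: 91–95%; Grade 2: 86–90%; Grade 3: < 85" (per cent).
- Hypotension, lowest grade: "Grade 0: systolic blood pressure (SBP) > 70% or 80/50 mm Hg before surgery". Next grade: "Grade 1: SBP < 70% or 80/50 mm Hg before surgery". Grade 2 has the same form with 60% and 70/40.

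Under Primary safety indicators a second system applies: "AEs are graded 1–5 according to the Common Terminology Criteria for Adverse Events 5.0". The article does not say how the two systems relate.

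The grades bear on reported results. The Abstract lists hypoxemia among the adverse reactions whose incidence is a primary endpoint. Primary safety indicators names both hypoxemia and respiratory depression. The Statistical analysis method section says that the incidence of adverse reactions will be calculated. Under Who will be blinded {17a}, only patients are blinded.

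**The concern.** A grading scale used to count cases has to give every possible reading one grade and only one. Where it does not, whoever completes the form decides. In this trial that person knows the treatment, and different sites may decide differently.

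The problem is worst where it lies between no event and event, because it then decides whether a patient counts as a case. Where it lies between two event grades, it changes recorded severity but not the any-grade incidence.

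Fewer adverse effects, including respiratory depression, are part of the Background's case for nalbuphine. An unclear case definition therefore adds noise, and room for bias, to a comparison that the trial is meant to inform.

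**Working it through.** There is no stated figure to reproduce. The check is to apply each scale literally to whole-number readings and list those that fall in no grade or in more than one.

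**Respiratory rate.** Grade 0 is above 12, Grade 1 is above 6 and below 12, Grade 2 is below 6.
- 12: not above 12 and not below 12, so no grade. It lies between no event and event.
- 6: not above 6 and not below 6, so no grade. It lies between two event grades, so only severity is affected.
- No reading falls in two grades.

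**SpO2.** The bands are 96–100, 91–95, 86–90 and below 85.
- 85: no grade. It lies between Grade 2 and Grade 3, so only severity is affected.
- No reading falls in two grades.
- The header codes are 1, 2, 3, 4; the defined grades are 0, 1, 2, 3. Matched by position, code 1 is Grade 0 (96–100%, normal). Matched by label, code 1 is Grade 1 (91–95%), normal has no code, and code 4 has no definition. The two readings give different any-grade counts.

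**Hypotension.** Let b be the preoperative systolic pressure and s the observed one. Only the systolic part of each absolute limit is used. The article gives no baseline pressures, so b is assumed. Taking *or* as written:
- Grade 0: s > 0.7b or s > 80, that is, s above the smaller of 0.7b and 80.
- Grade 1: s < 0.7b or s < 80, that is, s below the larger of the two. There is no lower bound.
- Grade 2: s < 0.6b or s < 70, that is, s below the larger of 0.6b and 70.

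Readings strictly between 0.7b and 80, in whichever order these fall, meet both Grade 0 and Grade 1.

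| Assumed b | 0.7b | 0.6b | Grades 0 and 1 both met | of which Grade 2 also met |
|---|---|---|---|---|
| 100 | 70 | 60 | 71–79 | none |
| 120 | 84 | 72 | 81–83 | none |
| 140 | 98 | 84 | 81–97 | 81–83 |
| 160 | 112 | 96 | 81–111 | 81–95 |

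Example: with b = 140, a reading of 90 is above 80 (Grade 0), and 90/140 = 64.3% is below 70% (Grade 1). A reading of 82 is above 80 (Grade 0), and 82/140 = 58.6% is below both 70% and 60% (Grades 1 and 2).

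Using the relative limit alone removes the overlap of Grades 0 and 1 but not every fault: exactly 70% then has no grade, and anything below 60% still meets Grades 1 and 2.

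**Two systems side by side.** Primary safety indicators applies CTCAE grades 1–5 to adverse events. Observation of AEs grades respiratory depression 0–2 and hypoxemia 0–3. Neither section says which one defines a case for the incidence tables.

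**The case against.** The best answer is that this is a wording matter that a derivation rule can settle. Secondary safety indicators already requires respiration and blood pressure to be measured and respiratory and circulatory parameters to be monitored. Taking the worst grade would resolve every hypotension overlap, and a more severe grade nested within a milder one is ordinary. This largely stands, and it is why the fix is cheap. But the article states no such rule. The opposite reading, Grade 0 whenever either limit is satisfied, is equally literal and gives a different count. Nor is this detail left to an unseen analysis plan: the thresholds are stated, and a plan could apply them only by overriding them.

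Several stronger readings are tempting, and the documents do not support them.

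- *The safety rates cannot be computed.* They can, once a rule is fixed. The gaps at rate 6 and SpO2 85% do not touch any-grade incidence.
- *All three scales put readings in two grades.* Only hypotension does, and it is not among the reactions named in the Abstract or under Primary safety indicators.
- *The heart-rate scale is also faulty.* Its code 1 covers "heart rate less than 50 beats/min, more than 120 beats/min, or occurrence of arrhythmia" and its code 0 covers everything else, so each patient gets one code. Splitting that code would be a preference.
- *Mixing the CTCAE and fallback scales will misorder severe events.* The fallback applies only to events absent from the NCI list, and no section plans to pool the two.
- *CTCAE grading contradicts the observation scales.* The two can coexist; what is missing is the statement of how they relate.

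**Conclusion.** The point holds for three scales. Two of the faults can change whether a patient counts as a case of a named primary safety item: the missing grade at a respiratory rate of 12, and the mismatch between hypoxemia codes and grades. The third, the overlap of hypotension Grades 0 and 1, can change whether hypotension is counted. Its width depends on baseline pressure: 3 whole-number readings at an assumed 120 mm Hg (81–83), 17 at 140 (81–97) and 31 at 160 (81–111).

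These widths rest on assumed baselines, on the systolic limits alone and on a literal *or*. The documents give no distribution of respiratory rates or blood pressures, so the share of patients affected cannot be stated. For respiratory rate, a reading of 12 matters to case status only in a patient with no reading below 12. The analysis of effective analgesia is untouched.

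**What to change.** 1. Record the respiratory rate, SpO2 and blood pressure themselves, and derive the grades centrally by one rule.
2. Rewrite the three scales so that each possible value has exactly one grade: a closed inequality on one side of every boundary, hypoxemia header codes that match the grades defined below them, and one stated rule for combining the relative and absolute blood pressure limits (for example, that the worst grade applies). The clinical lead chooses the side of each boundary; this review takes no position on the cut-offs.
3. Reconcile Primary safety indicators with Observation of AEs, and say which scale defines a case in the reported incidences.

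The cost is a short amendment to the case report form guide and the derivation rules. Respiration and blood pressure are already measured, and the hypoxemia scale itself needs a saturation reading, so no new measurement is required. Patients already enrolled can be graded by the same rule wherever the underlying values were kept.
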